# A novel carbon-fibre adjustable reusable accessory (CARA) for supine breast positioning to reduce toxicity in breast adjuvant radiotherapy: a study protocol for a multicentre phase III randomized controlled trial

**DOI:** 10.1186/s12885-022-09759-y

**Published:** 2022-06-20

**Keywords:** Breast cancer, Supine positioning, Adjuvant radiotherapy, Skin toxicity, Moist desquamation, Infra-mammary fold, Breast support, Quality of life, Patient-reported outcomes

## Abstract

**Background:**

A novel device for supine positioning in breast radiotherapy for patients with large or pendulous breasts has been developed and tested in phase II studies. This trial is designed to assess the efficacy of the device to reduce skin toxicity and unwanted normal tissue dose in comparison to the current clinical standard for supine breast support during breast radiotherapy.

**Methods:**

Patients at high risk for moist desquamation, having infra-mammary fold or lateral ptosis, will be randomized into two arms. Patients in the control arm will receive breast radiotherapy with supine positioning using current standard of care. Patients in the experimental arm will be positioned supine with the novel device. The primary endpoint is the incidence of moist desquamation in the infra-mammary fold. We hypothesize a 20% reduction (from 50 to 30%) in the rate of moist desquamation in the study arm versus the control arm. For 80% power, two-tailed α = 0.05 and 10% loss to follow up, 110 patients will be assigned to each arm. The proportion of patients experiencing moist desquamation in the two arms will be compared using logistic regression adjusting for brassiere cup size, skin fold size, body mass index, smoking status, and dose fractionation schedule. An unadjusted comparison will also be made using the chi-square test, or Fisher’s exact test, if appropriate. Secondary endpoints include dose-volume statistics for the lung and heart, skin dose and clinical parameters including setup time, reproducibility, and staff experience with setup procedures. Patient-reported pain, skin condition interference with sleep and daily activities, and comfort during treatment are also secondary endpoints.

**Discussion:**

Based on results from earlier phase II studies, it is expected that the device-enabled elimination of infra-mammary fold should reduce toxicity and improve quality of life for this patient population. Earlier studies showed reduction in dose to organs at risk including lung and heart, indicating potential for other long-term benefits for patients using the device. This study is limited to acute skin toxicity, patient-reported outcomes, and clinical factors to inform integration of the device into standard breast radiotherapy procedures.

**Trial registration:**

Clinicaltrials.gov identifier: NCT04257396. Registered February 6 2020.

**Supplementary Information:**

The online version contains supplementary material available at 10.1186/s12885-022-09759-y.

## Background

The majority of patients with in-situ and early-stage breast cancer receive adjuvant breast radiation therapy (RT) after breast conserving surgery, with adjuvant RT reducing the relative risk of cancer recurrence by half to two thirds [1] while offering minimal overall toxicity, good cosmetic results, and improved quality of life [2].

Some breast RT patients experience skin toxicity [3], which may include moist desquamation (MD), a painful breakdown of skin that can impact quality of life [4]. Development of MD has been found to depend on multiple factors, including the skin dose, the presence of skin folds, breast size, breast ptosis, and body mass index (BMI). Several studies of supine breast RT using varying fractionation schedules, use of beam-modifying wedges or intensity-modulated radiation therapy (IMRT), all concur that the group expected to be at highest risk of MD consists of patients having prominent infra-mammary fold (IMF) areas, BMI greater than 30, brassiere cup size D or larger, and large mid-breast separation [5–8].

Various approaches to supine breast positioning for patients with large or pendulous breasts have been investigated [9]. Currently, there is no accepted standard for supine breast positioning supported by peer-reviewed evidence for large or pendulous breasts. Brassiere use in supine breast RT was reported to reduce lung and heart volume for left breast patients but resulted in higher rates of acute skin toxicity [10]. Thermoplastic shells have been reported to reduce heart dose for left breast patients who are not eligible for breath hold techniques, but this technique is problematic for very large patients and rate of occurrence and degree of MD has not been reported [11]. Prone positioning has also been investigated as a potential solution to the problem of skin folds for pendulous breasts [12–20]. While some success has been achieved in reducing lung dose and eliminating IMF, the prone technique is generally not suitable for patients requiring nodal irradiation and may increase dose to the heart in some treatment conditions. Moreover, the prone position is not tolerable for all patients. The risk of MD in the infra-mammary area for the large or pendulous breast population is expected to be up to 50% with standard supine positioning, even with IMRT, when the whole breast is treated.

Interpretation of study results with respect to MD is made challenging by the fact that in standard scoring systems, MD appears in both grades 2 and 3 (e.g., Radiation Therapy Oncology Group (RTOG) and National Cancer Institute – Common Terminology Criteria for Adverse Events (NCI CTCAE V5.0)). In addition, many studies do not document BMI or the presence of skin folds, and many studies do not monitor skin toxicity out to two weeks post-treatment when at least 10% of skin reactions peak [8] for standard fractionation schedules, which can result in under-reporting of MD.

In breast RT, skin dose depends on factors including the planning technique, dose constraints, dose prescription, and beam energy. Patients having skin folds during treatment are expected to develop MD in the fold because delivering the prescribed breast dose involves the skin fold dose reaching over 95% of the prescription dose, as it lies within the treatment volume. The risk of MD has also been linked with the volume of the treated breast receiving 105% or more of the prescribed dose (breast V105%) [21–23].

To reduce MD incidence in this patient population, a novel Carbon-fibre Adjustable Reusable Accessory (CARA) for breast support was designed, fabricated, and tested beginning in 2016 [24, 25]. The current CARA clinical prototype is shown in use on a patient in Fig. 1. In a pilot phase II trial using this first clinical prototype [26], 30 patients at highest risk for MD based on BMI, skin folds, and breast cup size underwent computed tomography (CT) simulation and treatment planning both with and without CARA. The first 10 patients were treated with current standard of care and the last 20 patients were treated using CARA V1.0. The clinical treatment planning volume dose constraint for the step and shoot (field-in-field) forward-planned IMRT technique for large breasts at the time was V107% < 20 cm3. There was no constraint on V105%. CT images of the patient in Fig. 1 are shown in Fig. 2 with and without CARA. Dose-volume statistics demonstrated a systematic reduction in medial–lateral breast separation and associated reductions in ipsilateral lung dose volume receiving 20 Gy or more (lung V20Gy, *p* = 0.005), volume of breast receiving 105% or more of the prescribed dose (breast V105%, *p* = 0.006) and volume of body treated (body V50%, *p* = 0.001) without compromising target coverage. All IMFs in this study were eliminated on CARA treatment plans. Peak skin reactions for the CARA treated group were 10% grade 1, 75% grade 2 and 15% grade 3 using CTCAE V4.0, and daily variation in treatment setup was consistent with standard supine positioning [26].

**Fig. 1 Fig1:**
[figure not shown]
Patient without CARA support (**a**) and with CARA support (**b**). The CARA carbon fibre cradle supporting the breast is visible

**Fig. 2 Fig2:**
[figure not shown]
Axial CT images of the patient shown in Fig. 1 without CARA (**a**) and with CARA (**b**). The tangential beams and target volume are shown

Following the phase II study, three significant changes were implemented to reduce the incidence of MD in the context of IMF removal using CARA. First, the CARA cradle was re-designed to remove dose due to scatter arising from the attachment to the supporting bracket, resulting in CARA V2.0. Second, the material system was re-designed to reduce the areal density of the entire carbon-fibre cradle by 50%, further reducing the expected skin dose by approximately 10% across all areas of the breast in contact with the cradle. The current version of the cradle, CARA V3.0, incorporates this modification. In addition, a sliding window IMRT technique has now been introduced for tangential breast irradiation. With the established benefits of removing the IMF and reducing breast separation using CARA, tighter dose constraints on V105% can now be met using the sliding window technique. An IMRT dose constraint of V105% < 2% of the optimization target volume (OTV) is now in use.

To address deficiencies in measuring MD using standard scoring systems [27] and to alleviate the difficulty in having patients return to the clinic multiple times post-RT, patient-reported outcomes (PRO) are now the primary measure. Patient-reported outcomes are recognized as important clinically relevant outcome measures in modern radiation oncology [28–31]. Our institution established and validated the Prospective Outcomes and Support Initiative (POSI) methodology to collect PRO information [32]. A recent study investigated PROs for degree and location of skin reaction, pain, sleep disruption, and activity interruption for patients receiving whole breast RT [33]. The sensitivity and specificity for patient-reported incidence of MD were 87% and 76% respectively using open skin as an indicator of MD. The PRO instrument used in that study is in use in this trial.

Having demonstrated the potential clinical benefit of CARA through reduction in doses to organs at risk (OARs) [26], the current study is designed to assess the effectiveness of utilizing CARA V3.0 to reduce the incidence of acute skin reactions in the IMF in patients at high risk of MD undergoing breast RT. In this protocol, the IMF refers to the areas of skin on the inferior breast surface and on the chest that are in contact when the breast is unsupported in the supine position. The IMF is effectively eliminated when using CARA, but skin reactions are being monitored on this skin area after removal of the breast support, post-RT delivery. Compared to the pilot phase II trial, this is a phase III randomized controlled trial (RCT) on a larger population that incorporates improvements from the pilot and the use of PROs for the primary outcome measure. In addition, a discussion of the clinical acceptability of CARA, with respect to workflow measures, setup reproducibility, and therapist satisfaction, will be provided.

## Methods/Design

### Objectives

The primary objective of this study is to determine whether CARA V3.0 can reduce the incidence of moist desquamation in the IMF for patients with large or pendulous breasts undergoing breast RT in the supine position.

The secondary objectives of the study are as follows:To assess whether the severity of MD in the IMF can be reduced using CARA V3.0.To assess whether overall breast skin reaction scores can be reduced using CARA V3.0.To assess if CARA V3.0 reduces the volume of ipsilateral lung receiving 20 Gy or more (V20Gy).To assess if CARA V3.0 can reduce or maintain the volume of heart receiving 25 Gy or more (V25Gy) for left breast patients.To assess if CARA V3.0 can reduce the volume of body receiving greater than 50% (V50%) and greater than 105% (V105%) of the prescribed dose.To determine a dose-area parameter that is predictive of MD.To compare workflow and breast position reproducibility between the two study arms.To compare the PROs for quality of life measures and comfort during treatment setup between the two study arms.To compare radiation therapist experience between the two study arms.

### Study design

This is a phase III multicentre trial with patients randomized to two treatment arms of equal sample size. Arm 1 (experimental arm) patients will receive CARA V3.0, while arm 2 (control arm) patients will be treated according to the current standard of care at the treatment centre (without CARA V3.0). The study schema is shown in Fig. 3.

**Fig. 3 Fig3:**
[figure not shown]
Study schema for each participant from identification and eligibility screening to study completion

### Primary endpoint and measures

#### Presence or absence of MD in the IMF

Based on the PRO questionnaire (described under *Data Collection* [see Additional file 1]), a positive score of MD in the IMF will be based on a response of “Yes” for open skin within the past seven days (Question 7a) and a non-zero response for “under the breast” as a location of open skin (Question 7b), unless MD is definitively ruled out by a trained and blinded staff assessor.

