### Data collection

#### Baseline assessment

Data collection activities are shown in Table 1. Patients will have a baseline assessment prior to the first treatment. Patient height and weight, BMI, age, smoking status, RT prescription (including boost), adjuvant chemotherapy, brassiere size (band and cup size), IMF skin fold depth in treatment position, and presence of other skin folds will be recorded. The skin will also be assessed at baseline for any pre-existing conditions such as erythema, telangiectasia, desquamation, or infection. At CT simulation, a baseline photograph of the IMF skin will be acquired as well as a photo of the patient in treatment position. A PRO questionnaire is also collected at baseline.

**Table 1 Tab1:** Schedule of activities and data collection

**Study Activity**	**New patient appointment with radiation oncologist**	**Prior to CT simulation**	**Prior to first treatment**	**Weekly during Breast RT**	**Post-RT weekly to 7 weeks from start of breast RT**
Introduction to study	**X**				
Inclusion/exclusion criteria screening	**X**	**X**			
Informed consent obtained		**X**			
Enrollment and randomization		**X**			
Baseline assessment			**X**		
Patient-reported outcome questionnaire			**X**	**X**	**X**
Skin assessment performed by staff			**X**	**Last week of RT, or for five-day fractionation, last day of RT**	**Optional per patient preference**
Skin dose measurement				**Up to three times per patient; optional for sites other than the coordinating site**	
Timing of clinical flow				**X**	
Standard imaging				**X**	
CBCT imaging				**Up to three times per patient**	
Therapist satisfaction				**Last week of RT, or for five-day fractionation, last day of RT**	

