#### Staff skin assessments

Staff radiation therapists, nurses, or radiation oncologists blinded to the treatment arm will perform skin assessments. Staff performing these assessments are required to undergo specific training for this purpose. An in-house MD scoring tool specifically for the IMF will be used in addition to CTCAE V4.0 skin toxicity criteria. Staff skin assessments are required at baseline and during the last week of treatment (or in five-fraction prescriptions, required on the last day of treatment). If the patient is able and willing, staff skin assessments will also be completed weekly thereafter, out to 7 weeks after the start of breast RT.

Each staff skin assessment includes taking photographs of the treated skin in the IMF. Photos of other areas of skin experiencing MD at the time of each assessment may also be acquired. For patients assessed remotely, the patient may be asked to provide photographs of their skin taken at the time of the assessment.

While the method of breast positioning (i.e., Arm 1 or Arm 2) will be open label to the patient and treating staff, it is preferred that staff performing the follow-up skin assessments be blind to which arm of the study participants are in and not have access to the randomization allocation data. If this is not possible (such as in smaller centres), one additional trained study member will perform blinded assessment using photographs taken of the treated IMF area. If there is disagreement between the two assessments, a third trained study member will perform blinded assessment using the photographs. The final assessment of the primary outcome will be by majority vote.

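### The protocol gives two inconsistent rules for the primary endpoint: a patient report that only a blinded assessor may overrule, and a staff majority vote that can include an unblinded reading

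*Protocol article*

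**What the plan says.** **Endpoint rule** (Primary endpoint and measures, Presence or absence of MD in the IMF). A patient is positive if she answers yes to open skin in the past seven days (Question 7a) and gives a non-zero answer for the location under the breast (Question 7b), "unless MD is definitively ruled out by a trained and blinded staff assessor". The patient-reported outcome (PRO) is the base. The only exception is removal of a positive, and it is reserved for a blinded assessor.

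**Assessment rule** (Data collection, Staff skin assessments). The section opens by saying that blinded staff do the skin assessments, then weakens this: "it is preferred that staff performing the follow-up skin assessments be blind to which arm of the study participants are in". Where that is not possible, such as in smaller centres, one more trained person reads photographs blinded. If the two readings disagree, a third person reads the photographs blinded. Then: "The final assessment of the primary outcome will be by majority vote". The PRO is not mentioned.

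**Timing.** "Staff skin assessments are required at baseline and during the last week of treatment" (last day for five fractions). After radiotherapy, Table 1 lists staff assessment as "Optional per patient preference", while the PRO runs weekly to week 7. Positioning is open label to patients and treating staff.

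**Accuracy of the PRO** (Background). "The sensitivity and specificity for patient-reported incidence of MD were 87% and 76% respectively using open skin as an indicator of MD".

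**The concern.** The primary outcome needs a single definition. Here one section makes it a patient report that a blinded assessor may overrule, and another settles it by a vote of staff readings. Which applies to a given patient depends on how her centre is staffed. If the choice is left until adjudication, it will be made by people who may already know the data.

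Blinding is at stake too. The patient report is open label, and the blinded override is the safeguard against reporting influenced by knowledge of the arm. A vote that includes an unblinded reader puts knowledge of the arm into that safeguard.

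The second, smaller issue is who gets the override. After the mandatory end-of-treatment check, a report can be cleared only if the patient accepts an assessment, and she knows her arm. If acceptance differed by arm, clearing of false-positive reports would differ too, producing a difference between arms with no treatment effect behind it.

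**Working it through.** **1. The two rules side by side**, for a patient at a centre without a blinded on-site assessor:

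| PRO | Staff vote | Endpoint rule | Assessment rule |
|---|---|---|---|
| Positive | MD present | Event | Event |
| Positive | MD absent | Event, unless a blinded assessor definitively ruled it out | No event |
| Negative | MD present | No event | Event |
| Negative | MD absent | No event | No event |

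The third row is a direct contradiction. The second is one whenever the vote falls short of a definitive blinded exclusion, for example when it is carried two to one with the unblinded reader in the majority.

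**2. When the unblinded vote matters.** Let U be the unblinded on-site reading, B1 the first blinded photo reader and B2 the second.

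- U agrees with B1: no further reading is made, and the result equals B1.
- U disagrees with B1, and B2 agrees with B1: the result is the blinded readers' reading.
- U disagrees with B1, and B2 agrees with U: the blinded readers are split and U decides.

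Every result therefore has at least one blinded reader behind it. U tips the outcome only when the blinded readers split.

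**3. The plan's own sample size.** Inputs from Sample size calculation and recruitment period: 50% versus 30%, two-sided α = 0.05, 80% power.

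n = [1.96·√(2·0.40·0.60) + 0.8416·√(0.50·0.50 + 0.30·0.70)]² / 0.20² = (1.358 + 0.571)² / 0.04 = 93 per arm.

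This reproduces the stated figure and is not in dispute. Enrolling 110 with 10% loss leaves 110·0.9 = 99 evaluable per arm, which is used below.

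**4. Illustration of unequal clearing.** From the Background: sensitivity 0.87 and specificity 0.76, so false-positive rate 0.24. Assumed: true MD rate p = 0.40 in both arms; a share f of false-positive reports cleared by staff; no true positive cleared. The documents give no value for f.

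Observed rate = 0.87·p + 0.24·(1 − p)·(1 − f) = 0.348 + 0.144·(1 − f)

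With d the difference in observed rates a and b, and p̄ their mean:

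s0 = √(2·p̄(1 − p̄)/99), s1 = √(a(1 − a)/99 + b(1 − b)/99)

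Rejection probability = Φ((d − 1.96·s0)/s1) + Φ((−d − 1.96·s0)/s1)

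For 40% versus 60%: a = 0.348 + 0.144·0.6 = 0.4344; b = 0.348 + 0.144·0.4 = 0.4056; d = 0.0288; s0 = 0.0702; s1 = 0.0701. The result is Φ(−1.55) + Φ(−2.37) = 0.060 + 0.009 = 0.069.

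| Cleared, control vs CARA | Observed rates | Spurious difference | Type I error | Type I error if false-positive rate were 0.12 |
|---|---|---|---|---|
| 45% vs 55% | 42.7% vs 41.3% | 1.4 points | 5.5% | 5.1% |
| 40% vs 60% | 43.4% vs 40.6% | 2.9 points | 6.9% | 5.5% |
| 30% vs 60% | 44.9% vs 40.6% | 4.3 points | 9.4% | 6.1% |
| 20% vs 70% | 46.3% vs 39.1% | 7.2 points | 17.5% | 8.1% |

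The last column halves 0.24 as a further assumption, because the quoted specificity is for open skin alone and the endpoint also requires the location item. Swapping the arms gives the same type I error with the spurious difference against CARA.

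**The case against.** **The vote may only settle the staff reading.** It stands under Staff skin assessments, so it could be read as feeding the override and not as replacing the PRO. That is plausible, but the text says the primary outcome, not the staff reading. Even on this reading, an unblinded vote enters a step that the endpoint section reserves for a blinded assessor.

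**The reach is limited.** The vote applies only where a blinded on-site assessor is not possible, and no result stands without a blinded reader behind it. Both points hold. A reader might infer that the unblinded assessor controls the outcome whenever the first blinded reader agrees; in that case the outcome is simply the blinded reader's own.

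**The one-way override is not an error.** A reader might infer bias because a staff-detected case in a PRO-negative patient is not counted. The protocol explains why the PRO is primary, and specificity is the weaker of its two quoted properties, so an override aimed at false positives is defensible. With equal sensitivity in both arms, missed cases dilute the contrast and do not bias it.

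**Unequal clearing is hypothetical.** A reader might infer that the type I error is inflated to 9% or 17.5%. Nothing in the documents shows that uptake will differ by arm, or in which direction. Every patient in both arms has a mandatory check at the end of treatment, which the illustration does not model separately. Nor is 24% an established false-positive rate for this endpoint. With a 10-point gap in clearing, the error is close to nominal.

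What remains is that assessment after that check is voluntary. The gap is longest for the five-fraction schedule, where the check falls on the last day of treatment and the PRO continues to week 7.

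**Conclusion.** Wrong as written. The two sections define the primary endpoint inconsistently, and the protocol does not say which governs. This rests on the text alone and needs no numerical assumption. How many patients are affected cannot be computed: it depends on how many are treated at centres without a blinded on-site assessor and how often blinded photo readers split, and the protocol gives neither.

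Unequal clearing of false-positive reports is a secondary vulnerability and not a demonstrated bias. Its size runs from 5.5% type I error (45% versus 55% cleared) through about 7% and 9% to 17.5% (20% versus 70%). These figures are conditional on assumed clearing shares, a true rate of 40% in both arms, the quoted sensitivity and specificity carrying over to this endpoint, and 99 evaluable patients per arm. The documents do not support saying that the type I error is inflated, only that the plan leaves this route open.

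**What to change.** State one rule in both sections:

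- The PRO decides (Questions 7a and 7b). A positive is overruled only by blinded readings that cover the same seven-day window.
- Where on-site staff are not blinded, only the blinded photo readers already provided for count, and the on-site reading has no vote. If the blinded readers do not agree that MD is absent, it has not been definitively ruled out and the PRO positive stands. This also supplies the tie-break.
- Delete the majority-vote sentence or rewrite it to match, and reconcile the opening statement that assessors are blinded with the later one that blinding is preferred.
- Request the existing remote or photo assessment from every PRO-positive patient in both arms, so that access to the override does not rest on patient preference alone.
- Report a sensitivity analysis on the PRO alone, without any override.

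Staff-detected MD in PRO-negative patients should not be added to the primary endpoint. After radiotherapy it would be found only in those who chose to be assessed, which brings selective ascertainment back in the other direction. It can be a sensitivity analysis.

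The cost is mainly wording, plus a photo request to PRO-positive patients and some further reading by the blinded readers already planned. It should be settled before any outcome is adjudicated, including for the interim analysis.
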